### Intervention strategy

The intervention strategy involves a community-based worker (the SPK) carrying out home visits with individual families and participatory meetings with groups of women, to improve health and nutrition in the first 1000 days of life. The SPK is responsible for two main activities: (a) conducting a single home visit to each pregnant woman in the third trimester of pregnancy with counselling on maternal nutrition, followed by monthly home visits to all children under two, with counselling for growth promotion; (b) a monthly participatory meeting with a local women’s group. The SPK uses a problem-solving approach in both of these activities: during home visits, she identifies each mother’s current concerns about illness, feeding and care, then discusses possible solutions and barriers to putting the solutions into practice. During participatory meetings, she helps groups to identify community level health and nutrition problems, and to find locally feasible strategies to address them. We developed materials for these activities using formative research data from a quantitative nutrition survey conducted in 2010 in the study districts, qualitative discussions with women’s group members and facilitators participating in previous community interventions, and early intervention piloting data.

We propose this strategy because the current evidence suggests that an integrated approach to prevent undernutrition is more likely to succeed than discrete interventions (e.g. handwashing promotion or micronutrient supplementation on their own) [33-40]. We hypothesise that, to maximise its benefits, the strategy should include ‘fast-acting’ components to address immediate determinants of undernutrition (e.g. enhanced prevention, detection and treatment for infections, improved feeding and care-giving practices), as well as ‘slow-acting’ components to influence underlying determinants (e.g. unsafe water and sanitation, access to family planning, women and girls’ empowerment). The intervention’s Theory of Change is described in Figure 3. A detailed description of intervention activities is given below, and a village-level view of activities is shown in Figure 4.

**Figure 3 Fig3:**
[figure not shown]
Theory of change.

**Figure 4 Fig4:**
[figure not shown]
A village-level view of the community intervention strategy.

#### Home visits

The SPK obtains the names and location of all pregnant women and children under two in her working area from the Anganwadi worker, women’s group members, and other community members. She visits all women at least once during pregnancy, and then visits all mothers of children under two on a monthly basis. At each visit to a mother and child, she asks about current or recent illness, takes a mid-upper arm circumference (MUAC) measurement for children over 6 months, then engages the mother in a dialogue about feeding, infection control, and care-giving practices. This dialogue starts with the mothers’ immediate concerns with illness, feeding and care, and then builds on the SPK’s own observations of the mothers’ behaviour with her child and of the household (e.g. water use, mosquito net availability) to further guide the counselling session. The SPK is aided by picture cards depicting good practices and containing prompts for recommendations tailored to the local context. Depending on the child’s age and MUAC status, the SPK can take one of four approaches:Child visited is younger than 6 monthsThe SPK responds to the mothers’ immediate concerns, provides appropriate breastfeeding counselling and, if the infant is ill, arranges to visit the Auxiliary Nurse Midwife or nearest appropriate health facility.Child visited is older than 6 months, ill, and with green or yellow MUAC (≥115 mm)If the child is ill, the SPK gives recommendations on feeding during illness, checks the Mother Child Protection card – which contains records of immunisations - and asks about deworming, iron and vitamin A supplementation, Then, together with the mother, she makes a plan to visit the Auxiliary Nurse Midwife, Anganwadi, or the most appropriate local health facility.Child visited is older than 6 months, not ill, with green or yellow MUAC (≥115 mm)The SPK asks about current child feeding practices, including what kinds of foods are given, in which frequency and quantity, then discusses how to use locally available foods in specific recipes to increase the nutrient and energy density of complementary foods, and demonstrating these in the mother’s home. The SPK then discusses the importance of handwashing and offers advice to improve the hygiene of food preparation and feeding. She also discusses and demonstrates childhood stimulation techniques with the mother or family.Severely malnourished (MUAC <115 mm and/or bilateral pitting oedema)The SPK refers all severely malnourished children to the *Anganwadi* and assists with onward referral to Nutrition Rehabilitation Centre (NRC). She visits children with Severe Acute Malnutrition (SAM) following their discharge from the MTC and counsels the mother on feeding the child for recovery.

We chose to use MUAC as a screening tool because monthly weight measurement is collected by the existing *Anganwadi*. In addition, national and international evidence remains unclear about the actual benefit of plotting weight for growth promotion, and a critical review found that measuring and recording left little time for counselling and problem-solving with mothers [41]. Community-based management of acute malnutrition programmes commonly use MUAC to screen children over six months for moderate and acute malnutrition. This method is easily accepted by community health workers, and MUAC < 115 mm is a better predictor of mortality risk in malnourished children than weight-for-height < −3 [42].

We chose a guided but flexible approach to counselling for two reasons. Half of children under two in the study districts are underweight and over 60% are stunted [13]. Doing triage based on wasting or underweight to identify which prevention and treatment measures to discuss during home visits seemed superfluous, as most mothers would require counselling. Using strict algorithms for counselling also implies a strong reliance on job aides and standardized messages. While these are helpful and used to some extent in this intervention, we felt that it would be more empowering to give the SPK a basic sequence for the session (i.e. discussing illness, feeding, infection control and care-giving), along with picture cards containing key messages, but also give them the freedom to use their judgment and local knowledge to adapt the session to each mother.

#### Participatory meetings with women’s groups

The SPK also carries out a cycle of 20 monthly participatory meetings with groups of women, focusing on maternal and child health and nutrition. These meetings primarily target pregnant and lactating mothers, mothers of children under two, and adolescent girls (see Figure 5). They are however open to other community members because our previous experience with groups shows that this is important for inclusion and dissemination of information. The groups follow a four-phase participatory learning and action cycle to: (1) assess the health and nutrition situation; (2) decide on actions to take; (3) take action; (4) evaluate the process. In the first phase, the SPK introduces groups to the meeting cycle. Groups play a participatory game to discuss which mothers do not receive health and nutrition entitlements, discuss reasons for this and invite those mothers to join the meetings if they are not already attending. In the next meeting, the SPK describes the intergenerational cycle of undernutrition using a pictorial diagram and encourages the group to discuss local views and practices relating to undernutrition. Groups play a picture card game to identify health, feeding and caregiving problems related to undernutrition. The problems highlighted in the game are pre-identified by the study team on the basis of formative research. Group participants are invited to prioritise the problems that they would like to address by voting using the picture cards. In the second phase, groups explore the causes of their prioritised problems. They do this by listening to stories created by the SPKs using local themes. The stories illustrate how health and nutrition problems are linked to underlying household, community-level and health-service related issues. Group members discuss these underlying causes, then decide which of them they want to address and how. They allocate responsibilities for each strategy, decide on indicators to measure progress, and plan a community meeting to share their strategies with other community members and enlist their support. In the third phase, group members implement and review the strategies they have decided upon. At this time the SPK also introduces group members to other positive strategies for them to try at home, including how to enhance the density and diversity of complementary foods using local products and practice responsive feeding. In the fourth and final phase, group members discuss the progress of their strategies and share achievements and difficulties encountered during the meeting cycle. It is anticipated that the SPKs will coordinate at a full meeting cycle in the course of the trial, resulting in a range of individual, household and community-level strategies.

**Figure 5 Fig5:**
[figure not shown]
Women and girls discuss the benefits of working as a group.

##### Recruitment, supervision and training of intervention workers

In the intervention arm, we recruited 60 SPKs through consultation with local Village Health Sanitation and Nutrition Committees (VHSNCs) and *Anganwadi Sevikas*. The SPK’s working area is her own village and its attached hamlets. She is paid a monthly stipend equivalent to that of existing *Anganwadi Sevikas.*

Six supervisors recruited by the study team support 10 SPKs each. SPKs and their supervisors receive phased trainings and attend bi-monthly supervision meetings. For home visits, training sessions covered knowledge and skills for counselling to improve Infant and Young Child Feeding practices, care-seeking for common childhood illnesses, and household-based strategies to prevent illness including handwashing, safe handling of water and food, and disposal of faeces. The training preparing SPKs for participatory group meetings included practical sessions on conducting women’s group meetings using a participatory learning and action approach, as well as interacting with existing community health workers.

##### Strengthening Village Health Sanitation and Nutrition Committees (VHSNCs)

In both intervention and controls arms, we will seek to strengthen the capacity of VHSNCs, which are village-level, government-mandated bodies responsible for assessing community health needs, preparing and implementing village health plans, and monitoring the provision of local health and nutrition services under NRHM. We will hold eight quarterly participatory meetings with VHSNCs over a period of two years. These meetings will involve participatory discussions to sensitise members to issues related to inequity and exclusion from health and nutrition services and entitlements, as well as identifying and addressing gaps in health and nutrition services. Ekjut have developed meeting plans and tools for engaging with Village Health Committees in Jharkhand, Odisha, and Madhya Pradesh. We propose to undertake this activity as a minimum common service to intervention and control areas because it has potential for long-term benefit and the work of VHSNCs can be sustained beyond the trial period at no added cost to local health services.

### Research questions

#### Primary research question

What is the impact and cost-effectiveness of a community strategy with participatory women’s groups and home visits, on linear growth among children 0–18 months in rural India?

#### Secondary research questions

Does the strategy lead to improvements in feeding, infection control and caring practices for children 0–18 months?Does the strategy lead to increases in food intake and dietary diversity for women during pregnancy and lactation?What operational factors affect the strategy’s delivery and impact?What are the potential scalability, operational requirements, cost and impact of the strategy beyond the trial area?

### Sample size

The primary outcome of the study is mean length for age Z (LAZ) score at 18 months. In a meta-analysis of complementary feeding trials testing interventions to improve growth, nutrition education interventions had a mean effect size of 0.2 Z scores on LAZ at 18 months (range 0.04, 0.64) [38]. We therefore chose 0.15 as a conservative estimate of the effect size. The intra-cluster correlation (ICC) for stunting was estimated at 0.035 using an analysis of 42 DHS studies and our own data from the study areas [43]. The unit of randomisation (cluster) is a village and its attached hamlets. We expect around 25 live births per year in each cluster. Accounting for 10% attrition due to loss to follow-up and mortality, recruiting all eligible children born over 12 months in 110 clusters (2772 children before and 2520 after attrition), will allow us to detect a difference of 0.15 in mean LAZ scores between intervention and control arms (SD of 1) with 80% power and alpha of 0.05, and a design effect (D) of 1.8, calculated as D = 1 + (25–1) x 0.035. This sample size also gives the trial 80% power to detect a 13% reduction in the prevalence of stunting (from 60% to 52.5%), a 19% reduction in the prevalence of wasting (from 40% to 32.5%), and a reduction in the infant mortality rate greater than 45% (from 100 to 55 per 1000 livebirths) [44]. To account for the possibility of clusters dropping out of the study and for attrition rates exceeding our 10% estimate, we enrolled a total of 120 clusters (villages).

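### The 80% power for mean LAZ rests on an ICC labelled as being for stunting; if that ICC is on the yes/no scale, power is about 69% to 73%, depending on cluster layout

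*Protocol article*

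**What the plan says.** All of this is in the Sample size section of the protocol article.

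- Outcome: "The primary outcome of the study is mean length for age Z (LAZ) score at 18 months".
- Effect: "We therefore chose 0.15 as a conservative estimate of the effect size".
- Clustering: "The intra-cluster correlation (ICC) for stunting was estimated at 0.035", drawn from 42 DHS surveys together with the team's own study-area data.
- Design effect: "calculated as D = 1 + (25–1) x 0.035", printed as 1.8 and applied to the LAZ power statement: "with 80% power and alpha of 0.05, and a design effect (D) of 1.8". The assumed SD is 1.
- Numbers: 110 clusters, "2772 children before and 2520 after attrition", with a 10% attrition allowance.

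The section then claims 80% power from the same sample for a fall in stunting from 60% to 52.5%. It enrols 120 clusters, keeping the extra ten against cluster drop-out and attrition above 10%. It gives no ICC for LAZ and shows no power at any other ICC.

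**The concern.** Stunting is LAZ cut at a threshold. Cutting a continuous variable discards information, and for a normal variable the ICC of the yes/no version is smaller than that of the variable itself. Putting a stunting ICC into the design effect for mean LAZ therefore understates the clustering and overstates the power.

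There is almost no headroom. The design effect at which 2520 children give exactly 80% power is about 1.81, and the plan prints 1.8. The assumed effect is also small, and the cited meta-analysis range begins at 0.04, so a null or borderline result is plausible. Such a result would be read against a power claim of 80%.

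**Working it through.** **Inputs from the Sample size section.** Difference 0.15; SD 1; alpha 0.05 (sidedness not stated, two-sided assumed); N = 2520 analysed, equal arms; ICC 0.035; 25 births per cluster; 110 clusters planned and 120 enrolled; stunting prevalence 60%.

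**Step 1: reproduce the plan.** Unclustered n per arm = 2(1.96 + 0.8416)² / 0.15² = 697.7, rounded up to 698. Total with D = 1.8: 698 × 1.8 × 2 = 2513. With D = 1 + 24 × 0.035 = 1.84: 2569. Power = Φ(0.15/√(4D/N) − 1.96), with N = 2520:

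- D = 1.8: 0.15/0.05345 − 1.96 = 0.846, power 80.1%.
- D = 1.84: 0.15/0.05404 − 1.96 = 0.816, power 79.3%.

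The stated 80% is what the stated inputs give.

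**Step 2: convert the ICC.** For a normal variable cut at prevalence p, the yes/no ICC is approximately the continuous ICC × φ(z_p)² / [p(1 − p)]. At p = 0.60, z = 0.2533 and φ(z)² / 0.24 = 0.622. So 0.035 / 0.622 = 0.0563; solving the bivariate normal exactly gives 0.0562. The prevalence hardly matters: the exact value runs from 0.055 at 50% to 0.058 at 65%.

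**Step 3: recompute the power, N = 2520.** The plan's formula uses m = 25, whereas 2520/110 = 22.9 and 2520/120 = 21, so three layouts are shown.

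| Layout | ICC 0.035 | ICC 0.045 | ICC 0.056 | Detectable difference at 0.056 |
|---|---|---|---|---|
| Plan's formula, m = 25 | D 1.84, 79% | 74% | D 2.35, 69% | 0.171 |
| 110 clusters of 22.9 | D 1.77, 81% | 76% | D 2.23, 71% | 0.167 |
| 120 clusters of 21 | D 1.70, 82% | 78% | D 2.12, 73% | 0.163 |

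The last column is 2.8016 × √(4D/N). Within each layout, moving the ICC from 0.035 to 0.056 costs 9 to 10 points.

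**Step 4: headroom.** 80% power needs D ≤ 2520 / (2 × 697.7) = 1.806. The LAZ ICC must then be no more than 0.806/24 = 0.034, 0.806/21.9 = 0.037 or 0.806/20 = 0.040 in the three layouts.

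**Step 5: attrition.** 2772 × 0.9 = 2495, not 2520. The plan multiplied (2520 × 1.1 = 2772) where dividing gives 2520/0.9 = 2800. With 2495 children and D = 1.84, power is 78.9% against 79.3%.

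**The case against.** The strongest reply is that the text never states the scale on which 0.035 was estimated, and its sources are not available here. The article is loose with the word elsewhere: the Economic evaluation section calls cases of stunting prevented the primary outcome measure. If stunting stands here for LAZ, or the ICC came from a latent-scale model, no conversion is needed and 80% stands. This reply holds, and it is why the result is conditional. It does not remove the problem. The section applies the same sample to the stunting comparison, and the yes/no power there reproduces with the same design effect (81% at D = 1.8, 80% at D = 1.84). So 0.035 is serving as a yes/no ICC as well. Under a normal model one value cannot fit both scales: 0.035 for LAZ would imply 0.035 × 0.622 = 0.022 for stunting.

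It can also be said that 0.15 is cautious against the cited mean effect of 0.2. At 0.2, even with ICC 0.056, power is about 91% (D = 2.35) to 93% (D = 2.12). That is a fair comfort, but the stated claim concerns 0.15.

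A reader might infer more than the document supports:

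- *That the 80% is an arithmetic error.* It is not; Step 1 reproduces it. The doubt is about one input.
- *That power drops from 80% to 73%.* This compares different designs. The 73% uses all 120 clusters, where the starting figure is 82%.
- *That the assumed infant mortality of 100 per 1000 uses up the whole 10% attrition allowance.* The Trial participants section excludes neonatal deaths, so part of that mortality falls outside the eligible children. The ten reserve clusters are also there for excess attrition.
- *That rounding 1.84 to 1.8, or the attrition slip, matters materially.* Each moves power by less than one point.

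**Conclusion.** The point holds conditionally. The power for the continuous primary outcome is supported only by an ICC labelled for its dichotomised form, with no LAZ value and no sensitivity range. If the label is taken at face value, power for a 0.15 difference is about 69% by the plan's own formula, 71% for the planned 110 clusters at their analysed size, and 73% if 2520 children come from all 120. The difference detectable with 80% power is 0.16 to 0.17 rather than 0.15.

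This rests on 0.035 being a yes/no-scale ICC, on LAZ being approximately normal with about 60% below the stunting cut-off, on a two-sided 5% test and on equal cluster sizes. The direction follows from the first two assumptions, and the exact prevalence has little influence. Full conversion is not needed to fall short: an ICC of 0.045 already gives 74% to 78%. The consequence lies in how the result will be interpreted, not in how the trial is run.

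**What to change.** Restate the primary power using an ICC estimated for LAZ itself from the study-area data that the team says it holds. State the scale of that ICC, leave D unrounded, and give the number of clusters and the analysed cluster size. If no LAZ ICC can be obtained, report power as a range over ICC 0.035 to 0.056, for one named layout: about 69% to 79% by the plan's formula, 71% to 81% for 110 clusters of 22.9, or 73% to 82% for 120 clusters of 21. A single figure of 73% should not be printed, since it depends on both the unconfirmed conversion and the reserve clusters.

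Correct the attrition figures at the same time: 2772 less 10% is 2495, and 2520 after 10% loss needs 2800.

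The cost is a recalculation and possibly a less favourable stated power. The Interim analysis section reports that the recruitment target was reached in February 2015. No extra enrolment is needed, and nothing in the conduct or analysis changes.

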### Trial participants

Participants are women in the third trimester of pregnancy residing in the study clusters and identified between the 1st of October 2013 and 31st December 2015. Incentivised volunteers report every newly identified pregnancy to a member of the monitoring team. A study monitor then approaches the pregnant woman to explain the study and seek her consent for participation. Every pregnant woman residing in the study clusters and identified between the 1st October 2013 and 10th February 2015 is also asked for permission to follow-up her liveborn child for a period of 18 months. Pregnant women will be enrolled until the 31st December 2015 in order to measure the impact of the interventions on maternal nutrition in pregnancy.

We exclude stillbirths and neonatal deaths, infants whose mothers have died, infants with congenital abnormalities, multiple births, and mother/infant pairs who migrate out of the study area permanently during the study period. We define permanent migration as mother/infant pair missing more than two consecutive interviews (i.e. being absent from the study area for at least six months) at any point during the infant’s 18 months follow-up period.

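### In the 110-cluster sample-size calculation, the 10% allowance for deaths and loss to follow-up conflicts with the infant mortality of 100 per 1000 used in the same paragraph

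*Protocol article*

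**What the plan says.** All the sample-size figures are in the Sample size section of the protocol article.

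- The target is to "detect a difference of 0.15 in mean LAZ scores between intervention and control arms (SD of 1"; the power claimed for this is 80%, at alpha 0.05. The design effect is given as 1.8, "calculated as D = 1 + (25–1) x 0.035".
- The plan reaches this by "recruiting all eligible children born over 12 months in 110 clusters (2772 children before and 2520 after attrition", with around 25 live births expected per cluster per year.
- The step from 2772 to 2520 is described as "Accounting for 10% attrition due to loss to follow-up and mortality".
- A secondary power statement uses infant mortality going "from 100 to 55 per 1000 livebirths".
- The number of clusters was raised from 110 to 120 "To account for the possibility of clusters dropping out of the study and for attrition rates exceeding our 10% estimate".

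The Trial participants section adds exclusions: "We exclude stillbirths and neonatal deaths, infants whose mothers have died", and also congenital abnormalities, multiple births and permanent migrants. The Interim analysis section reports fewer live births than planned. It says recruitment was prolonged on the monitoring committee's advice until the target was met in February 2015, but gives no number for that target. The abstract puts participants at n = 2520.

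**The concern.** One 10% figure has to cover everything that removes a child before the primary outcome at 18 months. The paragraph's own infant mortality is already 10% by 12 months where the intervention has no effect. Nothing is then left for migration, missed 18-month visits, refusals or deaths in the last six months of follow-up.

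Two things are at stake. The printed analysable number for the primary outcome is too high on the plan's own inputs. The ten extra clusters, presented as cover for cluster drop-out and unusual attrition, would also have to carry ordinary loss to follow-up, because deaths have used the basic allowance.

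**Working it through.** **Inputs from the Sample size section.** Difference 0.15, SD 1, alpha 0.05 (two-sided assumed, as sidedness is not stated), power 80%, ICC 0.035, D = 1.8, 110 clusters in the calculation and 120 enrolled, around 25 births per cluster per year, 2772 before and 2520 after attrition, infant mortality 100 or 55 per 1000. **Assumption not in the document:** a further 5 to 10% of survivors lost.

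**1. The plan's figure reproduces.** Per arm without clustering, 2 x (1.96 + 0.84)² / 0.15² gives 698. Then 2 x 698 x 1.8 = 2513, against 2520 stated. The formula for D gives 1 + 24 x 0.035 = 1.84. Power at 2520 is 80.1% with D = 1.8 and 79.3% with D = 1.84.

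**2. The inflation step.** 2520 x 1.10 = 2772, whereas 2520 / 0.90 = 2800. The allowance in 2772 is therefore 1 − 2520/2772 = 9.09%.

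**3. Deaths alone, 110 clusters.**
- 100 per 1000 in both arms: 2772 x 0.90 = 2495, which is 25 short of 2520 with no other loss.
- 100 and 55 per 1000, mean 7.75%: 2772 x 0.9225 = 2557. The further loss tolerated is 1 − 2520/2557 = 1.5%.

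**4. Adding the assumed further loss, starting from 2772.** N = 2772 x (1 − mortality) x (1 − loss). D = 1 + (N/k − 1) x 0.035 for k clusters. Power = Φ(0.15/√(4D/N) − 1.96).

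| Mortality | Further loss | N analysed | Power, k = 110 | Power, k = 120 |
|---|---|---|---|---|
| 7.75% | 5% | 2429 | 80.1% | 81.5% |
| 7.75% | 10% | 2301 | 78.9% | 80.3% |
| 10% | 5% | 2370 | 79.5% | 81.0% |
| 10% | 10% | 2245 | 78.3% | 79.7% |

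The analysed number is 4 to 11% below 2520. If D is held at 1.8, power over the same four rows is 75.5 to 78.7%.

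**5. What 120 clusters offer if each yields 25 births.** 120 x 25 = 3000, and 1 − 2520/3000 = 16% total attrition is tolerable.
- Mortality 10%: 2700 survive, and 1 − 2520/2700 = 6.7% further loss is tolerable.
- Mortality 7.75%: 2768 survive, and 8.9% further loss is tolerable.
- At 5% further loss, 2565 or 2629 are analysed. At 10% further loss, 2430 or 2491.
- Over these four cases power is 81.5 to 83.2% with D recomputed, or 78.7 to 81.8% with D held at 1.8.

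Of the 3000 − 2520 = 480 children of margin, deaths take 300 at 10% mortality or about 233 at 7.75%.

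**6. Births needed for 2520 analysed.** 2520 / [(1 − mortality)(1 − loss)] gives 2875 (7.75%, 5%), 2947 (10%, 5%), 3035 (7.75%, 10%) and 3111 (10%, 10%).

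**The case against.** **Eligible children may already exclude neonatal deaths.** The calculation counts eligible children, and the Trial participants section removes neonatal deaths, congenital abnormalities and multiple births. On that reading only later deaths draw on the 10%, and the mortality figure does not exhaust it. This has some force, since around 25 births per cluster is approximate. But 110 x 25 = 2750 live births is already just under 2772, so 2772 looks like a count of live births before any exclusion. If exclusions do come first, the difficulty moves to the number of births: 2772 eligible children would need more than about 25 births per cluster in the stated 12 months. The narrower reading does not clearly rescue the figure.

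**The 120 clusters were enrolled for this purpose.** This largely stands. A reader might infer that 2520 cannot be delivered at all. The documents do not support that: 3000 births tolerate 16% total attrition, and recruitment was extended. Even the 110-cluster calculation reaches 2520 with mortality of 100 and 55 per 1000 if other losses are at most 1.5%. Two limits remain. The same margin must also cover cluster drop-out, and the reported shortfall in births weakens the figure of 25.

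**Recruitment to a fixed number.** A reader might also infer that recruitment stopped at a fixed count of births, so that the extra clusters added no children and are no reserve. The Interim analysis section gives no number for the target and does not say whether it counts births, enrolled or analysed children. Recruitment is elsewhere defined by dates. If the target was 2520 enrolled, deaths alone would leave 2268 to 2325. The assumed further loss would leave 2041 to 2208, with power of 77.4 to 79.3% at 120 clusters. That is a reason to ask which number was meant, not a finding.

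**Conclusion.** The point holds for the 110-cluster calculation. The step from 2772 to 2520 is not supported by the mortality in the same paragraph, and multiplying by 1.10 makes the real allowance smaller than the stated 10%.

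The consequence is modest. With 2772 births and 120 clusters, power stays at about 80 to 82%. This rests on the assumed 5 to 10% further loss, the ICC of 0.035, and D recomputed for the smaller clusters. What needs correcting is the printed analysable number and the account of what the extra clusters are for, not the size of the trial. It should not be claimed that the enrolled trial cannot reach 2520, or that the ten extra clusters provide no margin.

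**What to change.** In the Sample size section:

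1. Replace the single 10% with two components: deaths at the plan's own rate, and other losses (migration, missed visits, refusal). Apply them by division, not by multiplying by 1.10.
2. Restate the expected analysed number: about 2245 to 2430 of 2772 if 5 to 10% of survivors are lost, or the figure that follows from the investigators' own estimate of loss.
3. Give power for the 120 clusters enrolled, with D recomputed.
4. State whether the target reached in February 2015 was 2772 or 2520 children, and whether these are births, enrolled or analysed children.
5. Say that the assumed mortality is expected to absorb much of the margin from the extra clusters.

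The cost is a rewording of one paragraph and a less favourable analysable number. No extra enrolment and no change to the analysis is needed.
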